##### Number of behavioral health EBPP available to justice-involved individuals (county level)

Mental health EBPPs were taken from treatment recommendations for justice-involved individuals [39–45] and from community standards for treatment of serious mental illness posttraumatic stress disorder, borderline personality disorder, suicide thoughts or behaviors, anxiety, insomnia, and pain [46–52]. Substance use EBPPs were taken from the US National Institute on Drug Abuse’s consensus list [53]. Using the EBPP list described above, we ask whether each EBPP is available to justice-involved individuals in the county. If any of the respondents answers “yes”, we count that EBPP as being available to justice-involved individuals in the county.

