#### Survey respondents

The overall sample is 475 Stepping Up counties and 475 comparison counties. In each county, we will survey the administrators of community mental health, jail, probation, and community substance use treatment agencies (i.e., up to 4 respondents per county and ~ 3800 total; see Table 2). These respondents were selected because the jail and probation systems have the majority of individuals under justice control in a county, and mental health and substance use treatment administrators are responsible for the provision of behavioral health services for justice-involved individuals in the community.

**Table 2 Tab2:** Targeted type and number of survey respondents

Respondent type	Estimated number
Community mental health administrators	950
Jail administrators	950
Probation administrators	950
Community substance use treatment administrators	950

Note: The total survey population may be less than 3800 because some counties have the same person filling multiple roles listed above

To compile the respondent list, the research team developed a database of all Stepping Up and matched comparison counties. NACO-CSG-APAF provided a list of county contacts for Stepping Up counties. We contacted these individuals to provide the appropriate contact information for jail, probation, mental health, and substance use administrators in their county. We also conducted web-based searching. For comparison counties, we identified county-level experts through web-based searching. When contact information was not publicly available, we called individual agencies to identify the correct respondents. We also engaged in a snowball technique, in which we contacted experts already identified for assistance in identifying other possible respondents in their county.

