##### System integration (agencies nested within counties)

 is a dichotomization of the NCJTP Relationship Assessment Inventory [38] total score (i.e., excluding the additional items). Counties with scores of 18 or more are considered to have achieved “system integration”. A secondary (county level) measure will reflect the degree to which each of 12 listed behavioral health screening and assessment instruments are used by and/or shared among multiple responding agencies within a county. For each of the 12 instruments listed, counties will receive a score (0 = no agencies use the same instrument, 1 = two agencies use the same instrument, 2 = three agencies use the same instrument, and 3 = all four agencies use the same instruments).

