### Power analyses

The expected sample (475 paired counties, up to 4 respondents per county, resulting sample size of ~ 3800) and the response rate of 50% gives an expected sample of 1900 respondents. Given that anywhere from 0 to 4 respondents may complete the survey in any given county, with a 50% overall response rate, we anticipate that 712 counties will have at least one respondent who completes the survey. We used a conservative (higher than expected) intraclass correlation coefficient of 0.1 for addressing clustering of agencies within counties.

For county-level analysis, an effect size of 0.2, power of 0.8, confidence level of 95%, and statistical significance level of 0.05 were used to calculate the minimum sample size. Repeated measures analysis required a minimum total sample size of 304 counties. For logistic regression and other nonlinear predictive models, depending on the type and quantity of variables used in the model, the minimum total sample size required varied between 156 and 489 counties. With attrition, our calculations showed a power of 0.9 and more for most county-level analyses.

For agency-level analysis, a conservative agency-level effect size estimate (*d* = 0.1), a power of 0.8, confidence level of 95%, and significance level of 0.05 were used to calculate the minimum required sample size. Repeated measures analysis comparing respondents from Stepping Up and comparison counties resulted in a minimum sample size of 524 respondents. When comparing the response measures, measured at the agency level, over time, a minimum sample size of 1200 respondents is required. For predictive logistic regression and other nonlinear predictive models, the minimum sample size varied between 673 and 1100 respondents. Given the larger sample size of this study, our calculations showed a power higher than 0.9 for agency-level analyses.

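### The county EBPP count and the shared-instrument score rise with the number of responding agencies, so response patterns that differ by group can pass for a programme effect

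*Protocol article*

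**What the plan says.** All references are to the protocol article.

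- **EBPP count** (section on the number of behavioral health EBPP available, county level). Respondents say whether each listed practice is available in their county. If any one says yes, "we count that EBPP as being available to justice-involved individuals in the county". Table 1 lists this outcome as secondary. Aim 2 (Secondary) tests whether it improves faster in Stepping Up counties, and Aim 1b uses it as an outcome in the mediation analyses.
- **Shared-instrument score** (System integration). For 12 screening and assessment instruments, the county is scored on how far each is "used by and/or shared among multiple responding agencies within a county". The top levels are "2 = three agencies use the same instrument, and 3 = all four agencies use the same instruments". This is a secondary measure of system integration.
- **Response** (Power analyses). The plan expects that "anywhere from 0 to 4 respondents may complete the survey in any given county", and "the response rate of 50% gives an expected sample of 1900 respondents".
- **Covariates** (General approaches). The list is the Wave 1 value, months since joining, the matching score, and two indicators for administrators shared with other counties. The number and type of responding agencies are not on it.
- **Missing data.** The plan is recontact of respondents, multiple imputation within waves, and GEE or weighted GEE across waves. None of these is tied to the two scores.
- **Recruitment** (Survey respondents). For Stepping Up counties the programme organisations supplied contacts, and web searching was added. "For comparison counties, we identified county-level experts through web-based searching".

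**The concern.** Each score mixes what a county has with how many of its agencies answered. A county with four respondents has four chances of a yes on each EBPP; a county with one has one chance. A match on an instrument cannot be seen with a single respondent, so under the stated levels that county scores 0 whatever it really uses.

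The planned comparison is a difference between groups in rate of improvement. If comparison counties lose respondents faster than Stepping Up counties, their counts fall relative to Stepping Up with no change in services, and the result reads as faster improvement in Stepping Up counties. The union rule also hides the problem. It returns a complete-looking county value whenever one agency answers, so a weight for missing county values would not register an absent agency. At stake are one of the three named implementation outcomes, its use in the mediation analyses, and a secondary mechanism measure.

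**Working it through.** **1. The plan's own figures.** 3800 × 0.5 = 1900 respondents, which reproduces. For counties with at least one respondent, independent response at 50% gives 950 × (1 − 0.5⁴) = 890.6, not the stated 712. The stated figure matches 950 × 0.75 = 712.5, or a within-county correlation of response near 0.45. That mismatch is a separate matter; the point here does not depend on it.

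**2. Spread of respondents per county.** Independent response at 50% puts about 59, 238, 356, 238 and 59 counties at 0, 1, 2, 3 and 4 respondents. One-respondent counties are then 237.5 / 890.6 = 27% of those responding. A beta-binomial fitted to the stated 712 gives 0.1705 / 0.7495 = 23%. Either way the number varies widely.

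**3. Dependence of each score on the number k of respondents.**

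- *EBPP count.* If each respondent says yes with probability p, independently, P(counted) = 1 − (1 − p)^k. The document does not give p. For k = 1 to 4:
  - p = 0.1: 0.10, 0.19, 0.27, 0.34
  - p = 0.3: 0.30, 0.51, 0.66, 0.76
  - p = 0.5: 0.50, 0.75, 0.88, 0.94
  - p = 0.3 with within-county correlation 0.5: 0.30, 0.41, 0.47, 0.51. Agreement between respondents shrinks the effect but does not remove it.
- *Shared instruments.* The maximum total is 12 × (k − 1) = 0, 12, 24, 36 for k = 1 to 4. This needs no assumption beyond the stated levels. With each agency using an instrument with probability 0.3 (assumed), the expected totals are 0, 1.1, 2.9 and 5.3.

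**4. Effect on the group comparison.** A null simulation of the EBPP count used 475 against 475 counties, no programme effect and no true change, with 1000 runs per scenario. Assumed inputs: 30 items, p = 0.3, between-county SD 0.6 on the logit scale, independent respondents redrawn at each wave, complete cases, no imputation. Two tests at nominal 5% were run: the Wave 3 minus Wave 1 change, and Wave 3 adjusted for Wave 1.

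| Response over the three waves (Stepping Up / comparison) | Change score: false effect, rejection | Wave 1-adjusted: false effect, rejection |
|---|---|---|
| 50% steady / 50% steady | 0.01, 4.7% | 0.01, 5.3% |
| 60-50-40% in both | 0.00, 5.4% | 0.00, 4.8% |
| 50% steady / 50-47.5-45% | 0.73, 33.1% | 0.73, 43.1% |
| 50% steady / 50-45-40% | 1.40, 83.5% | 1.38, 92.4% |
| 55% constant / 45% constant | −0.03, 5.0% | 0.75, 45.8% |

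A hand check agrees. Averaged over responding counties at p = 0.3, P(counted) is 0.510 at 50% response, 0.484 at 45% and 0.460 at 40%. So 30 × (0.510 − 0.460) = 1.5 and 30 × (0.510 − 0.484) = 0.78, close to the simulated 1.40 and 0.73. The simulation also has between-county spread.

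**5. Why a constant gap matters only with Wave 1 adjustment.** In a change score the gap subtracts out. In the adjusted model the group effect is gap − b × gap, where b is the within-group slope on Wave 1, and b is below 1 when the score is noisy. At 55% against 45% the level gap is about 30 × (0.536 − 0.484) = 1.6 EBPPs, and roughly half of it (0.75) remains.

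**The case against.** **Both scores are secondary.** This stands. The primary implementation outcome (clients served) and the primary mechanism (the Performance Monitoring measure) are not union scores. A reader might infer that the main results are compromised; the document does not support that.

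**A fall in response over the study would be enough to mislead.** A reader might infer this, but it is wrong. The planned contrast is between groups, and a fall common to both gave rejection rates at the nominal level. A constant gap is also harmless in a pure change contrast. Nor does a difference in level at one wave show bias in a rate of change.

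**The document predicts no response gap.** This also stands. Web searching was used in both groups, agency calls and snowball contacts are not described as limited to one, and a single administration procedure applies to everyone. The programme's contact list, supplied for Stepping Up counties only, makes unequal response plausible and no more.

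**Multiple imputation may deal with it.** It would help only if absent agencies' answers are imputed before the county is scored. The article does not state the level of imputation, and a fuller analysis plan may do so. The scoring rule itself is stated, however, and it works from whoever answered.

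**The sizes rest on assumptions.** They do: list length, p, spread and response patterns are not in the document. If the same agencies answered at every wave, b would be larger and the constant-gap bias smaller. The direction of dependence on k does not rest on those values.

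**Scoring of one-respondent counties is not spelled out.** A score of 0 is an inference from the stated levels, though no higher level could be reached.

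**Conclusion.** The point holds in a limited form. Under the stated rules both scores can only stay level or rise with the number of responding agencies, and no listed covariate captures that number or the mix of agency types. A false programme effect arises if response changes differently by group across waves, or if it differs constantly by group and the contrast is read from a model adjusted for the Wave 1 value, as planned. The article gives no model equation, so which column of the table applies cannot be settled from it.

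Under the assumed inputs, a comparison-group drift of five points over the study raises the false-positive rate from 5% to 33% (change score) or 43% (adjusted). A ten-point drift raises it to 84% or 92%, with a false effect of about 1.4 EBPPs of 30. A constant gap of 55% against 45% gives 5% or 46%. These figures shrink if respondents within a county agree closely. The document does not show that such response patterns will occur. Severity: should-fix.

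**What to change.** **EBPP count.** In the county-level analysis, adjust for the number and type of responding agencies at each wave. Add one sensitivity analysis: either restrict to the same agency types responding at all waves, or fit a respondent-level model with agency-type effects and a county random effect.

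**Shared instruments.** Score the proportion of responding agency pairs that use the same instrument, and set one-respondent counties to missing, not 0.

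**Imputation.** If absent agencies' answers are to be imputed before scoring, say so.

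**Cost.** This changes analysis wording only and uses data already collected. One-respondent counties (about 23% to 27% of responding counties at 50% response) drop out of the shared-instrument measure. The respondent-level model estimates reported availability, not county availability. Respondent number at later waves may itself be affected by participation in Stepping Up, so adjustment is not neutral: report results with and without it. The choice should be fixed before any group comparison is seen.

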##### Resources for behavioral health EBPP for justice-involved individuals (agency level)

Respondents will be asked to report whether their agency has experienced an increase (+ 1), no change (0), or decrease (− 1) in funding from the prior year in 13 different areas (e.g., “screening and assessment”). We will cluster these 13 areas using factor analysis and then create total scores for each factor, which will serve as primary outcome/s. Initially, we planned to assess the total dollar amount of resources devoted to behavioral health services for justice-involved individuals, but found that most agencies could not report this number. Secondary measures relate to capacity and training: (1) the proportion of staff in clinical roles, (2) how many staff participated in behavioral health-related training in the past year, and (3) number of staff hired minus the number who left in the prior year. Lastly, we will use the NCJTPS’s Assess Your Resources scale [38], which uses Likert scale items, to measure respondent perceptions of the adequacy of resources available in their agency.

#### Aim 3: characterize implementation processes and critical incidents

##### Qualitative

We will use qualitative data to triangulate quantitative findings, enrich our understanding of how the target mechanisms work and lead to outcomes and critical incidents to EBPP implementation success or failure. Qualitative data will include interviews with 30 of the 475 county pairs (60 paired counties total). County pairs were randomly selected at Wave 1 (stratified by small, medium, and large county populations) and followed longitudinally at Waves 2 and 3. We anticipate 180 qualitative interviews (60 respondents at 3 time points). We will alternate CJ and behavioral health respondents to obtain multiple perspectives on the county’s progress. Respondents will be invited for interviews regardless of their survey status (i.e., completed, not yet completed, declined) for that wave.

*Fidelity to Stepping Up/Quantitative characterization of implementation strategies and sub-strategies used* to improve mental health or substance use services for justice-involved individuals and/or to reduce the number of people with mental illness in jail (agencies nested within counties). We will use a checklist with strategies and their descriptions constructed from the six main Stepping Up strategies as well as categories conceptualized by Powell [54] and the CJ-IIM [17]. Respondents will select whether anyone in the county is “planning to address this”, “some progress made”, or “significant progress made” using each strategy.

### Power analyses

The expected sample (475 paired counties, up to 4 respondents per county, resulting sample size of ~ 3800) and the response rate of 50% gives an expected sample of 1900 respondents. Given that anywhere from 0 to 4 respondents may complete the survey in any given county, with a 50% overall response rate, we anticipate that 712 counties will have at least one respondent who completes the survey. We used a conservative (higher than expected) intraclass correlation coefficient of 0.1 for addressing clustering of agencies within counties.

For county-level analysis, an effect size of 0.2, power of 0.8, confidence level of 95%, and statistical significance level of 0.05 were used to calculate the minimum sample size. Repeated measures analysis required a minimum total sample size of 304 counties. For logistic regression and other nonlinear predictive models, depending on the type and quantity of variables used in the model, the minimum total sample size required varied between 156 and 489 counties. With attrition, our calculations showed a power of 0.9 and more for most county-level analyses.

For agency-level analysis, a conservative agency-level effect size estimate (*d* = 0.1), a power of 0.8, confidence level of 95%, and significance level of 0.05 were used to calculate the minimum required sample size. Repeated measures analysis comparing respondents from Stepping Up and comparison counties resulted in a minimum sample size of 524 respondents. When comparing the response measures, measured at the agency level, over time, a minimum sample size of 1200 respondents is required. For predictive logistic regression and other nonlinear predictive models, the minimum sample size varied between 673 and 1100 respondents. Given the larger sample size of this study, our calculations showed a power higher than 0.9 for agency-level analyses.

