## Methods

County matching and baseline covariate controls increase the rigor for this longitudinal natural experiment, which is described consistent with STROBE guidelines [25] (see Supplemental Materials). The study will measure target mechanisms and key outcomes in 475 Stepping Up counties and 475 matched counties at three waves: study baseline, 18 months, and 36 months. Since counties self-select to be in Stepping Up, we cannot randomize counties to the Stepping Up Initiative. Instead, we use a case-matched design using the Centers for Disease Control and Prevention (CDC) peer counties methodology to identify non-Stepping Up comparison counties with similar size, demographics, and health, economic, and justice indicators [26–28]. Stepping Up began in 2015 and has been registering counties over time. Therefore, at study baseline, the 475 Stepping Up counties had been participating in Stepping Up from 1 to 5 years. Wave 1 (i.e., baseline) values and months since each county began Stepping Up will serve as covariates. Therefore, analyses examine differences between groups in within-county rates of change between study waves controlling for Wave 1. Our quantitative survey results will be augmented with qualitative interviews with 60 counties at each wave to enrich our understanding of how the implementation mechanisms work.

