### Analysis plan

#### General approaches

Primary tests will be 2-sided with α = 0.05. Analysis approaches accommodate nested and repeated measures data. We will examine predictive associations between Stepping Up membership, hypothesized target mechanisms, and implementation outcomes over time. We will use general linear models and generalized linear mixed models (GLMM) when the dependent variables are continuous and noncontinuous, respectively. GEE will be used instead when distributional assumptions are not met. For non-aggregated dependent variables reported at the agency level (i.e., hierarchical data), a random intercept growth hierarchical linear model (GHLM) will be fitted. All analyses will covary: (1) Wave 1 (baseline) values of dependent variables, (2) months since the county joined Stepping Up, (3) the matching score, (4) an indicator representing whether a the county shares their mental health administrator with other counties, and (5) a similar indicator for shared justice roles across counties.

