#### Aim 2: comparison of implementation outcomes between Stepping Up and non-Stepping Up counties

##### Primary

We will test the hypothesis that Stepping Up counties will show faster rate of improvement in the number of justice-involved clients receiving behavioral health services than will comparison counties, using GLMM and GEE. Analyses will test for differences in slopes (rates of change) between the two sets of counties.

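### The agency-level minimum of 524 respondents does not follow from the stated d = 0.1, so the claim of power above 0.9 at that effect is not supported as written

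*Protocol article*

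**What the plan says.** All the figures are in the Power analyses section of the protocol article. For the agency level, the inputs are "a conservative agency-level effect size estimate (*d* = 0.1), a power of 0.8, confidence level of 95%, and significance level of 0.05". From these the article reports that "Repeated measures analysis comparing respondents from Stepping Up and comparison counties resulted in a minimum sample size of 524 respondents". It gives a separate minimum of 1,200 respondents for comparing agency-level measures over time. It expects 1,900 respondents (50% of about 3,800), says that an ICC of 0.1 was used for agencies within counties, and concludes that "our calculations showed a power higher than 0.9 for agency-level analyses". On the number of responding counties it says "we anticipate that 712 counties will have at least one respondent who completes the survey".

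Three other statements bear on the check. General approaches says "Primary tests will be 2-sided with α = 0.05" and that every analysis adjusts for the Wave 1 value. Methods says "The study will measure target mechanisms and key outcomes in 475 Stepping Up counties and 475 matched counties at three waves", so the groups are equal and there are three measurements. The primary analysis under Aim 2 says "Analyses will test for differences in slopes (rates of change) between the two sets of counties". The article gives no between-wave correlation and no attrition rate for the agency-level figures.

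**The concern.** A between-group effect of 0.1 SD is very small. A single-wave comparison would need about 3,140 respondents in total, and averaging three correlated waves reduces that only in part. A minimum of 524 is therefore far too low on its face.

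The power statement depends on minima of this kind, because it is justified by the expected 1,900 being larger than them. If a minimum belongs to an effect twice the stated size, readers are told that the study can detect 0.1 SD with power above 0.9 when the calculation may only show this for 0.2 SD. That affects how a null result on an agency-level measure would be interpreted.

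**Working it through.** **Inputs.** From the article: d = 0.1; power 0.80; alpha 0.05 two-sided; two equal groups; three waves; 1,900 expected respondents; 712 responding counties; ICC 0.1. Assumed, because not given: the between-wave correlation rho, shown over a range and taken as equal between all pairs of waves.

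**1. Minimum sample for the between-group comparison (mean of three waves).**

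N = 4(1.960 + 0.8416)² / d² × (1 + 2·rho)/3. The first factor is 4 × 7.849 / d², which is 3,139.6 at d = 0.1 and 784.9 at d = 0.2.

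| rho | N at d = 0.1 | N at d = 0.2 |
|---|---|---|
| 0 | 1,047 | 262 |
| 0.3 | 1,674 | 419 |
| 0.5 | 2,093 | 523.3, i.e. 524 |
| 0.7 | 2,512 | 628 |

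The stated 524 is reproduced at d = 0.2, rho 0.5, with no clustering (526 if a noncentral F is used instead of the normal approximation). At d = 0.1 the smallest value, at rho = 0, is already 1,047. With 524 respondents, power at d = 0.1 is 0.51 at rho 0 and 0.29 at rho 0.5.

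**2. The stated ICC.** Respondents per responding county = 1,900/712 = 2.67. Design effect = 1 + (2.67 − 1) × 0.1 = 1.167. Applied at rho 0.5, d = 0.2 would need 523.3 × 1.167, about 611, and d = 0.1 would need 2,093 × 1.167, about 2,443. The ICC is therefore not visible in 524.

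**3. Power with 1,900 respondents at d = 0.1.** Effective N = 1,900/1.167 = 1,628. Power = Φ(0.1 / √(4V/1,628) − 1.96), where V is the variance of the contrast per respondent in SD² units:

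- mean of three waves: V = (1 + 2·rho)/3
- slope, as a 0.1 SD difference in change over 36 months: V = 2(1 − rho)
- mean of the two follow-up waves adjusted for baseline: V = (1 + rho)/2 − rho²

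| rho | Mean of 3 waves | Slope | Baseline-adjusted mean |
|---|---|---|---|
| 0.5 | 0.70 | 0.52 | 0.81 |
| 0.7 | 0.62 | 0.74 | 0.92 |
| 0.8 | 0.58 | 0.89 | 0.98 |

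The mean of three waves passes 0.9 only if rho is below about 0.08 (about 0.18 if clustering is ignored). The slope passes 0.9 at rho of about 0.81. These figures are before attrition and apply the same design effect to every contrast.

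**4. Could another model give 524 at d = 0.1?** The slope contrast needs 3,139.6 × 2(1 − rho), which equals 524 at rho of about 0.92. The baseline-adjusted mean gives 520 at rho 0.88. Both need a very high correlation, and neither is the plain group comparison that the sentence describes. A group-by-time test with f = 0.05 would give 524 near rho 0.6, but that f corresponds to a divergence of about 0.24 SD at 36 months, not 0.1.

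**5. Responding counties.** Independent 50% response from four people gives 950 × (1 − 0.5⁴) = 890.6, about 891. The stated 712 equals 950 × (1 − 0.5²) = 712.5, the result for two people per county.

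**The case against.** The strongest defence is that the article condenses a fuller protocol and need not print rho, and that the power claim depends on rho. This stands for power. A reader might infer that power above 0.9 is not delivered, or that the slope test is close to a coin toss. The documents do not support either as a general statement. The slope result is near one half only at rho 0.5 and passes 0.9 at about 0.81. The plan adjusts for Wave 1, and the baseline-adjusted mean reaches 0.92 at rho 0.7. The defence does not rescue 524, because no non-negative rho produces it for the comparison named.

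A reader might also infer that 524 and 1,200 contradict each other. That depends on what the comparison over time means. If 1,200 refers to the difference in slopes, d = 0.1 gives 1,200 at rho 0.81 without clustering (0.84 with it), and 1,900 respondents would then have power of about 0.94. The conflict is not established.

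Entering 0.1 as f instead of d is inference. The article names no software or settings, the match requires dropping the ICC, and the same settings do not give the county-level minimum of 304, which at d = 0.2 would need rho of about 0.08.

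On 712, the note to Table 2 says one person may fill several roles, and response may cluster within counties, so 891 is not necessarily right. A response correlation of about 0.45 would yield 712. Using 712 is also mildly conservative: 891 counties would give a design effect of 1 + (1,900/891 − 1) × 0.1 = 1.11 and slope power of 0.90 instead of 0.89 at rho 0.8.

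Finally, the Measures section labels the primary outcome as agencies nested within counties, with a county focus. It is therefore not certain that the agency-level paragraph is meant to cover the Aim 2 primary test.

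**Conclusion.** The point holds for the sample size. At the stated d = 0.1, 80% power and two-sided 0.05, the three-wave group comparison needs at least 1,047 respondents and about 2,093 at rho 0.5 (about 2,443 with the plan's ICC). At rho 0.5 that is four times the printed 524. This conclusion requires only that rho is not negative.

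For power the conclusion is narrower: the claim of more than 0.9 at d = 0.1 is not supported as stated. It may be true for some contrasts at high rho, but not for the comparison to which 524 refers unless rho is close to zero. The sizes given assume equal correlations between waves, a design effect of 1.167 and no attrition.

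The 712 figure is secondary: it does not follow from four independent respondents at 50%, and its basis is not given.

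**What to change.** Correct the Power analyses section without changing the sample:

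- State whether 0.1 is d or f. Either relabel the effect behind 524 as d = 0.2 (f = 0.1), noting that this figure omits the ICC, or keep d = 0.1 and restate the minimum as about 2,093 respondents (about 2,443 with the ICC) at rho 0.5.
- State rho, the design effect and the assumed attrition, and say which contrast lies behind 524 and which behind 1,200.
- Replace the statement of power above 0.9 with the power of the planned baseline-adjusted slope contrast at d = 0.1, over a stated rho range, with ICC and attrition applied.
- Correct 712, or state the response clustering or shared roles that produce it.

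The cost is recalculation and rewording. The number of counties, the measures and the analyses stay as they are. The reported agency-level power may become less favourable.
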